### Study procedures

The clinical trial procedures (enrollment, intervention and assessments) are detailed in Table 1. Eligible parents who agree to participate in the project (informed consent) will complete baseline in-person questionnaires in the place where the sessions will be held. After that, they will be randomly assigned to either the intervention program condition (TIK) or the control condition. Participants in the intervention group will start TIK sessions within 1 month following the baseline assessment and will complete post-intervention and follow-up (2-month post-intervention) assessments in person. At 2-month post-intervention, a booster session will be held at the same location the sessions took place immediately after participants complete the protocol evaluation. According to the original TIK structure, this booster session is offered as an optional follow-up to consolidate skills [10]. In the present clinical trial, we chose to include this session not only to minimize parents’ attrition but also to provide participants with an additional opportunity to practice skills and discuss challenges beyond completing questionnaires. Participants in the control group will complete the same evaluation protocol at equivalent assessment time points, in the same setting as the intervention sessions, but on different days to minimize contamination between study arms. In the case of both parents participating, each will complete an evaluation protocol independently. The facilitators will complete questionnaires during the intervention (after each session) and at the end of each facilitated group assessing implementation fidelity.

**Table 1 Tab1:** Clinical trial procedure

Variables	Informant	Measures	Enrollment and screening	Baseline [T0]	Allocation	During intervention	Post-intervention [T1]	2-month Follow-up [T2]
Eligibility screening	Parent	-	*					
Informed consent	Parent	-	*					
Sociodemographic and clinical data (parent and child)	Parent	Questionnaire developed for this study		*				
	Facilitators	Questionnaire developed for this study		*				
Process evaluation								
Fidelity	Facilitators/independent observer	TIK fidelity checklist				*		
Feasibility	Parent	Questionnaire developed for this study					*	
Attendance and retention of participants in the intervention	Facilitators	Facilitators’ records				*		
Acceptability	Parent	Questionnaire developed for this study					*	
Outcome evaluation								
Primary outcomes								
Parental emotion socialization								
Parents’ reactions to children’ emotions	Parent	CCNES		*			*	*
Parents’ beliefs about children’ emotions	Parent	PBACE		*			*	*
Parental emotion regulation	Parent	IM-P		*			*	*
Self-regulation	Parent	DERS-SF		*			*	*
Secondary outcomes								
Child								
Emotional/behavioral problems	Parent	SDQ-P		*			*	*
Emotional regulation	Parent	ERC		*			*	*
Parent/Legal guardian								
Parenting stress	Parent	PSS		*			*	*
Depressive symptoms	Parent	HADS - D		*			*	*
Parenting self-efficacy	Parent	MaaP		*			*	*

‘Parent’ refers to parents and legal guardians

*CCNES* Coping with Children’s Negative Emotions Scale, *PBACE* Parents’ Beliefs About Children’s Emotions Questionnaire, *SDQ-P* Strengths and Difficulties Questionnaire – Parent, *ERC* Emotion Regulation Checklist, *DERS-SF* Difficulties in Emotion Regulation Scale - Short Form, *PSS* Parental Stress Scale, *HADS-D* Hospital Anxiety and Depression Scale - Depression Symptoms, *MaaP* Me as a Parent Questionnaire, *IM-P* Interpersonal Mindfulness in Parenting Scale

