#### Acceptability of the intervention

TIK’s acceptability will be evaluated at the end of the program. Participants will be asked to complete a questionnaire composed of 16 questions answered on a Likert-type scale ranging from 1 (*not at all*) to 5 (*very much*), covering: (a) overall satisfaction with TIK; (b) if TIK meets parents’ expectations and contributes to improvements in their confidence as parent, in their relationship with their children, in their children well-being, and in their capacity to understand their children’s emotions and how to manage them; (c) the frequency to which they apply TIK contents on their daily interactions with their children; (d) the adequacy of the number, frequency and length of the sessions; (e) satisfaction with the group format; (f) perception of TIK’s facilitators competence and intervention’s facilities; and (g) usefulness of acquired strategies for parenting in the long-term. Participants will also be asked to report if they would recommend the program to other parents on a yes/no scale, as well as to rate the degree of facility/difficulty in understanding the concepts of emotion coaching and in applying emotion coaching strategies on a daily basis, using a Likert-type scale ranging from 1 (*very easy*) to 5 (*very difficult*). They will also be asked to answer three open-ended questions to report on the most and least useful aspects of the program, and if there were other contents that they would like to address in the program. A last open-ended question inquires about other suggestions for improving TIK.

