### Data management

Data management of this clinical trial will follow Lusófona University’s data protection policies and the General Data Protection Regulation (GDPR - UE, 2016/679). Research assistants will be responsible for data collection and data entry. Data from paper questionnaires will be entered on REDCap. By including range checks, field validation, mandatory fields, logic rules, and indicators of missing values, among other features, REDCap allows enhancing data quality in terms of its accuracy, completeness, and reliability. To maximize data accuracy, two independent research assistants will enter the same paper questionnaires into REDCap, which will compare the two entries and signal any discrepancy. Paper questionnaires will be kept at Lusófona University (access restricted), and any identifying data will be removed. Each participant will receive an ID code that would allow pairing data across assessment points. Pseudonymized data will be stored at Lusófona University server, after being encrypted and accessed by password, as well as signed consent forms. Only research assistants and project coordinators will have access to the data. Participants will have the right to access, change, or delete their own data at any time, as well as to remove their consent for participation, with no need for explanations. Data will be maintained for the time strictly necessary for achieving this project’s aims.

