### Nonadherence, attrition and missing data

Participants who discontinue attending TIK’s sessions will be invited to complete all outcome assessments, in-person, in a local of their preference. Participant’s attrition from the trial will be estimated through the number of participants who do not complete post-intervention and/or follow-up assessments. All participants who completed the baseline assessment will be considered in the analyses, irrespective of their adherence to the intervention, following intention-to-treat (ITT) principles to minimize attrition bias. Secondary sensitive analyses will be conducted to assess differences between intervention completers and non-completers participants in terms of sociodemographic and health characteristics. Moreover, if substantial non-adherence to the intervention is observed, a secondary and exploratory complier average causal effect (CACE) analysis will be undertaken to estimate the intervention effect among compliers (i.e., participants who attended at least 4 of the 6 sessions, including three of the four core sessions - sessions 2, 3, 4 or 5 - which is considered the minimum exposure to receive TIK core components).

Researchers will carefully check the questionnaires at the time of completion and alert participants whenever missing responses are identified. Nevertheless, if missing data are present in the predictor variables of the linear mixed-effects models, the pattern of missingness will be analyzed, and when MAR (Missing at Random) or MCAR (Missing Completely at Random), multiple imputation will be performed using *mice* package from R prior to fitting the linear mixed-effects models. Missing data in the outcomes are handled by the *lme4* package, since it uses all available data through its Maximum Likelihood estimation.

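### As written, the acceptability and barriers form is completed in person at T1 and falls under the on-the-spot missing-response check, so parents' opinions of TIK are not private from the research staff present.

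*Protocol article*

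**What the plan says.** All references are to the Protocol article.

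- **Mode and timing.** Under Study procedures, intervention-arm parents "will complete post-intervention and follow-up (2-month post-intervention) assessments in person". Table 1 lists acceptability and feasibility as parent questionnaires at T1, and the acceptability section agrees: "TIK’s acceptability will be evaluated at the end of the program".
- **Content.** The acceptability questionnaire has 16 items scored 1 to 5. They include "overall satisfaction with TIK" and "perception of TIK’s facilitators competence and intervention’s facilities". It also has a yes/no question on recommending the programme and open questions on its most and least useful aspects. The feasibility section adds two open questions on what helped and what hindered participation.
- **Medium.** Under Data management: "Data from paper questionnaires will be entered on REDCap".
- **Collection.** The same section says: "Research assistants will be responsible for data collection and data entry".
- **Check at completion.** Under Nonadherence, attrition and missing data: "Researchers will carefully check the questionnaires at the time of completion and alert participants whenever missing responses are identified". No questionnaire is excepted.
- **Protection.** Data management limits data access to research assistants and project coordinators. Ethics and dissemination says that paper forms carry a code and no direct identifiers, and that they are kept in a locked cabinet open to the principal investigator and two research fellows.
- **Analysis.** The process-evaluation part of Statistical methods plans means, standard deviations and frequencies per acceptability item, and a thematic analysis of the open answers.

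**The concern.** A parent who has just finished six group sessions is asked, face to face, to judge the programme and the people who ran it. A member of the research team then looks over the page while the parent is there. If the parent has left the facilitator rating or the question on least useful aspects blank, the procedure has the researcher point this out. A blank may be a polite way of not criticising, and the prompt can turn it into a polite answer.

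The efficacy scales are collected under the same check, but in both arms, with the control group completing the same protocol in the same setting. The acceptability form has no such counterpart: at T1 only the intervention arm has received TIK. A tendency to answer kindly would enter the reported item means, the proportion recommending TIK and the criticisms recorded in free text. No comparison within the trial could reveal it, and it could not be removed after collection. Acceptability is one of the two stated process aims. Process results will be discussed with community partners when deciding whether TIK should be changed for routine care, and family satisfaction also feeds the interim progress reports.

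**Working it through.** There is no figure in the plan to reproduce and no formula that applies. The check consists of reading the sections together.

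1. **Is the form completed in person?** Table 1 puts acceptability and feasibility at T1, and Study procedures makes the post-intervention assessment in person. Parents who stop attending sessions are also invited to complete their outcome assessments in person, at a place of their choice. Yes.
2. **Is it on paper?** Data management describes paper questionnaires that are double-entered into REDCap. The REDCap link mentioned under Participants enrollment and screening is for registering interest, and no electronic outcome form is described. Paper is the natural reading, although no sentence says it of this form alone.
3. **Does the check at completion cover it?** The sentence refers to the questionnaires in general and excepts none. As written, yes. This is a stated procedure whose wording reaches this form; it is not an inference from silence.
4. **Does the code give privacy?** Not at that moment, because the person checking the form has the parent in front of them. Nor does it fully do so later: the files linking identity to code are open to the principal investigator and to the two research fellows who handle recruitment and data collection.
5. **Who can see the answers?** Research assistants, research fellows, project coordinators and the principal investigator. Facilitators are not listed as collectors or as having access. The document does not say whether they are in the room while the form is filled in.
6. **Is there a comparator?** No. Only TIK recipients can rate TIK, and the planned summary is descriptive.
7. **Can the size be worked out?** No. The document gives no expected rating, no item standard deviation, no acceptability threshold and no alternative mode of completion with which to compare.

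Steps 1 to 4 establish that the answers are not private from the research staff present. Step 6 establishes that any resulting bias would be reported undiluted. Step 7 means that its size has to be left open.

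**The case against.** The case on the other side has substance.

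- **Purpose and place of the check.** It looks for gaps, not opinions, and the sentence leads straight into missing predictors and outcomes in the mixed models. The authors may have had only the efficacy scales in mind. The wording is nonetheless unrestricted, so the remedy is to restrict it.
- **Existing protections.** Forms are coded, access is limited, and confidentiality is explained before consent. All of this stands. It protects parents from facilitators and outsiders reading the data later; it does not protect them from the staff member checking the page.
- **Invitation to criticise.** The form asks for the least useful aspects, for difficulties in applying the strategies and for suggestions. That helps candour but does not supply privacy.
- **Condensed article.** Seating, form order and return procedure commonly sit in operational documents, and their absence here is not a fault. The point rests only on the check that the article does state.
- **Completeness.** The check protects against missing items, and giving it up for one form has a cost. This is a trade-off, not the correction of an error.

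Some stronger conclusions are tempting but unsupported:

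- A reader might infer that facilitators collect or read their own ratings. Data management and Ethics and dissemination point the other way.
- A reader might want to express the bias in standard errors, or say that an interval would miss the true mean. No confidence interval is planned for these items, and both the item standard deviation and the shift would have to be invented. Part of any courtesy effect would also arise on any form that can be linked to the parent, so the share due to the check is unknown.
- A reader might infer that the decision on changing TIK rests on these ratings. Patient and public involvement refers to process results broadly, and these also include fidelity, attendance, retention and barriers.

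**Conclusion.** The point holds as a cheap improvement to the process evaluation. Joined together, the sections place the acceptability and barriers form at an in-person assessment, on paper, under a check made by research staff in the parent's presence. The answers are therefore not private from those staff. That any resulting bias would be favourable is a reasonable inference about courtesy, not something the document states, and no size can be attached to it.

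The conclusion assumes that the general wording of the check means what it says for every questionnaire, and that this form is on paper like the rest. If the full protocol already exempts the form or has it returned sealed, the point is met and only the article's wording needs clarifying. The sample size and the efficacy models are not affected.

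**What to change.** Change two places in the plan.

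- **Nonadherence, attrition and missing data:** state that the on-the-spot check for missing responses does not apply to the acceptability and barriers form.
- **Acceptability of the intervention** (with a cross-reference from the feasibility section): state that this form is completed last, with facilitators not present; that the parent returns it in a sealed envelope bearing only the code, opened at data entry, or completes it through a coded REDCap link; and that parents are told facilitators will not see individual answers.

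The code keeps linkage to the other assessments, and sealed forms can still be double-entered. The cost is envelopes or one REDCap form, about a sentence in each place, and a few more unanswered items, which a descriptive item-by-item summary can tolerate. The form would still be linkable to the parent, so the change reduces the pressure to answer kindly without removing it altogether.

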### Participants enrollment and screening

Participants will be recruited through self-referral and referral processes from collaborating community partners (e.g., child welfare agencies, family support and counselling services, schools, local health center units) from the Lisbon Metropolitan Area or Lisbon District. Collaborating institutions will be requested to share the project with all parents via newsletter, personalized emails and putting up advertisement flyers in strategic locations. The dissemination materials will include a link available through REDCap (Research Electronic Data Capture) - a secure electronic data capture system designed to support data entry and management for research studies - through which parents can manifest their interest in being enrolled in the project. Interested parents could also contact the research team by email or telephone. Professionals working with families, namely those working with more vulnerable families (e.g., psychologists, social workers), will also have the opportunity to refer eligible parents to the clinical trial, based on their judgment that the family could benefit from participating in an emotion-focused group intervention. If they agree and consent, their contact details will be shared with the research team. Broader dissemination of the project will also take place through collaborating community partners’ social media (e.g., Instagram, Facebook), which will contain a link to be filled out by interested parents. A research team member will further contact all interested parents by telephone to assess their eligibility, discuss availability and logistical preferences (e.g., session schedule, site, and childcare needs), inform them of their eligibility status, and provide a full explanation of the clinical trial procedures (e.g., study aims, assessments, confidentiality and ethics issues, participants’ rights). Particularly, all participants will be informed that they will be randomly assigned to one of two groups, meaning that they could initiate the intervention within approximately one month or after 4–5 months (after the follow-up assessment), and that their participation involves no costs. Immediately after the telephone interview, written information about the clinical trial will be sent to parents by email, and if they agree to participate, parents will be asked to return their written informed consent via the same way. Following the provision of informed consent, parents will complete the baseline assessment protocol. Non-eligible parents will be informed about the reasons for their exclusion during the telephone interview, and those who require professional support will be advised or referred to specialized care by the research team. The expected completion date of recruitment is 28th February 2027.

### Sample size

Power analyses were conducted using Monte Carlo simulations for linear mixed-effects models in R (version 4.4.0) (packages *lme4* and *simr*). For each simulation, medium-sized interaction effects were specified, and different random intercept and slope variances were considered. Power for fixed interaction effects was evaluated using Wald *t*-tests; power to detect inter-individual variability in change over time was evaluated by comparing the models that include a random slope for time to reduced models including only a random intercept. These comparisons were performed using likelihood ratio tests. For primary analyses examining the time x group interaction effect on TIK’s efficacy, the simulation results indicated that, to achieve 80% power at *α* = 0.05, a total sample size of approximately 132 participants is required. Although the study is powered primarily to detect group × time effects and to account for significant inter-individual variability in change over time, exploratory moderation analyses to examine whether pre-test psychosocial risk is a moderator of TIK’s efficacy are also planned. With 132 participants, the power to detect a three-way group x time x psychosocial risk interaction is substantially lower, as expected (approximately 49%), and approximately 286 participants are required to achieve 80% power. Since we anticipate difficulties in recruiting such a large sample, in this trial, findings concerning the moderator role of psychosocial risk will therefore be interpreted cautiously and considered exploratory, while still providing valuable preliminary evidence regarding which families may benefit most from TIK. These results will help generate hypotheses and inform the design of future, larger implementation trials. Considering an attrition rate of 15% [46, 47], we will have to recruit approximately 152 participants to complete the baseline assessment.

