**Methods:**

This trial is a parallel two-arm randomized clinical trial, which includes both process (i.e., feasibility and acceptability) and efficacy evaluation (i.e., change in primary and secondary outcomes and moderated effects) of Tuning in to Kids^®^ in Portugal. A minimum of 152 parents/legal guardians (> 18 years old) with at least one child between 3 and 6 years old will be enrolled. Parents will be randomly assigned to the intervention group or waiting list control group (76 per condition), through blocked randomization, with allocation concealment. Participants in both conditions will complete self-report questionnaires assessing primary (parental emotion socialization) and secondary (parents and children functioning dimensions) outcomes at baseline, post-intervention, and follow-up (2 months post-intervention). Longitudinal data will be analyzed using linear mixed-effects models accounting for repeated measures within participants.

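### The recruitment target of 152 appears to add 15% to the required 132 instead of allowing for 15% loss from those recruited; it leaves about 129 expected completers, and 156 would be needed

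*Protocol article*

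**What the plan says.** The Sample size section of the protocol article derives its number by Monte Carlo simulation of linear mixed-effects models. For the time by group interaction, "to achieve 80% power at *α* = 0.05", it reports that "a total sample size of approximately 132 participants is required". It then allows for attrition in one sentence: "Considering an attrition rate of 15% [46, 47], we will have to recruit approximately 152 participants to complete the baseline assessment". No inflation formula is written out.

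The Methods part of the Abstract carries the same number as a floor, "A minimum of 152 parents/legal guardians", split evenly into 76 per condition.

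The section on nonadherence, attrition and missing data settles what attrition means here. It is counted from participants who miss the post-intervention assessment, the follow-up assessment or both. The same section keeps everyone who completed baseline in the analysis and relies on maximum likelihood to use whatever outcome data are available.

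**The concern.** The 152 are people who complete baseline, and attrition is counted among those same people afterwards. To have 132 left after a 15% loss, the required number has to be divided by 0.85. The stated target is lower than that and coincides with the result of multiplying by 1.15. Multiplication would be right only if the 15% were expressed as a fraction of the final sample, which the document does not say.

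At stake is whether the recruitment target meets the plan's own requirement under the plan's own attrition assumption. The sample-size justification will be carried into the trial report, where any reader can repeat this arithmetic.

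**Working it through.** **Inputs**
- Required number: 132 in total, 66 per arm at 1:1 allocation (Sample size; Trial design).
- Attrition: 15% (Sample size), counted after baseline (Nonadherence, attrition and missing data).
- Recruitment target: 152 (Sample size; Abstract), 76 per condition (Abstract).
- Power and alpha: 80% and 0.05 (Sample size). Sidedness is not stated; two-sided is assumed below.

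The 132 is taken as stated. It cannot be reproduced, because the article describes the simulation inputs only in words: "medium-sized interaction effects were specified, and different random intercept and slope variances were considered".

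**Reproducing the stated target**
- n × (1 + d) = 132 × 1.15 = 151.8, rounded up to 152. This matches.
- Per arm: 66 × 1.15 = 75.9, rounded up to 76. This matches.

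**Target with the loss taken from those recruited**
- n / (1 − d) = 132 / 0.85 = 155.3, rounded up to 156.
- Per arm: 66 / 0.85 = 77.6, rounded up to 78, again 156 in total.
- Check: 156 × 0.85 = 132.6, which meets 132.

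**What 152 delivers**
- Expected losses: 152 × 0.15 = 22.8.
- Expected completers: 152 × 0.85 = 129.2 (64.6 per arm), which is 2.8 below 132.
- Attrition at which 152 still leaves 132: 1 − 132/152 = 13.2%.

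**Size of the effect on power (worst-case approximation)**

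Suppose that 132 gives exactly 80% power and that dropouts contribute nothing. With a normal approximation, the non-centrality is 1.960 + 0.842 = 2.802 and scales with the square root of the number of completers.
- At 129.2: Φ(2.802 × √(129.2/132) − 1.960) = 79.2%.
- At 129: Φ(2.802 × √(129/132) − 1.960) = 79.1%.

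The loss is 0.8 to 0.9 percentage points.

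**The case against.** The strongest reply accepts the arithmetic and disputes its weight.

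- **Partial data are kept.** All baseline completers enter the mixed model, and a parent who misses only the follow-up counts as lost but still contributes baseline and post-intervention values. The analysed set is therefore 152, and the power figures above are a lower bound under their assumptions. This stands, and it makes the real loss probably smaller. It does not rescue the target: by inflating 132 for attrition, the plan treats 132 as the number wanted after losses. A parent lost before the post-intervention assessment also supplies no observed change.
- **Simulation error may be larger than the effect.** The number of simulation runs is not given. Assuming 500 to 5,000 runs, the Monte Carlo standard error at 80% power is √(0.8 × 0.2 / runs), or 1.8 to 0.6 points, so roughly ±3.5 to ±1.1 points at 95%. A loss below 1 point lies inside that range. This limits the practical consequence but does not change the step from 132 to 152.
- **The numbers are hedged.** The Sample size section calls both 132 and 152 approximate, and the Abstract's minimum does not prevent further recruitment. But a stated minimum that misses its own requirement under its own assumption is still wrong as written. The gap is 4 of 156, or 2.6%.
- **No formula is written.** This is true. Multiplication by 1.15 is an inference from the exact match, and the point should be worded that way. The shortfall does not depend on it, since 152 × 0.85 is below 132 however 152 was obtained.

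A reader might infer that the target, the per-condition number and the power claim all contradict one another. They do not: 152 and 76 per condition agree exactly. The only mismatch is between 152 with 15% attrition and the 132 required.

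**Conclusion.** The point holds as a small arithmetic error. Under the plan's own 15% attrition, counted after baseline, 152 recruits leave about 129 expected completers, about 3 fewer than the stated 132. The number that meets the requirement is 156, four more than planned.

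This rests on taking 132 as stated and on reading the 15% as a proportion of those who complete baseline, which is how the document defines attrition. The origin of 152 as 132 × 1.15 is a strong inference, not something the article states.

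It would be tempting to conclude that the trial is underpowered, or that its power is 79%. The documents support neither. The loss is at most about 1 percentage point in an approximation that discards all data from dropouts, whereas the planned analysis keeps those data. The 79% also does not come from the trial's own model, so it should not be quoted as the trial's power. The planned analysis itself is unaffected.

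**What to change.** Make one of two changes in both the Sample size section and the Abstract.

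1. Correct the target to 156, 78 per condition. This costs four more recruits, two per arm. Recruitment is expected to run until 28 February 2027, so there may still be room for it.
2. Keep 152 (76 per condition) and state that it retains 132 completers only if attrition is at most about 13%, with about 129 expected at 15%. This costs one sentence and no participants.

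Under the second option, do not insert a fixed 79% as the new power. If a power figure is wanted for 152, re-run the trial's own simulation with 152 recruits, 15% dropout and the planned all-available-data model, and report that result. This needs only computing time.
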